## Abstract

**Background:**

The World Health Organization (WHO) roadmap aims to control, eliminate, or eradicate neglected tropical diseases (NTDs) by promoting innovation in prevention, diagnosis, and treatment. In this context, mobile health (mHealth) tools could play an important role in improving health care across the globe, including for skin-related NTDs. One such tool is the WHO Skin NTDs App (currently available in its beta version), which utilizes artificial intelligence (AI) algorithms to classify skin lesion images and offers diagnostic suggestions and management information to bolster early detection at primary care levels. However, to harness the full potential of this and similar mHealth tools, additional insights into their diagnostic performance and potential implementation avenues in settings with limited access to trained dermatologists are essential.

**Objective:**

The objective of our mixed methods study is to test the functionality, operability, and potential of the AI-supported diagnostic component of the WHO Skin NTDs App (beta version) to support the detection of skin NTDs and common skin conditions in Senegal.

**Methods:**

We are conducting a diagnostic accuracy study combined with a qualitative preimplementation usability exploration. For the quantitative component, we will collect and analyze approximately 800 skin lesion images from patients presenting to the dermatology unit at the Thiès regional hospital in Senegal. Each lesion will be independently assessed by the AI-based WHO Skin NTDs App and by a dermatologist who will provide a diagnosis serving as the reference standard. Performance metrics, including accuracy, sensitivity, specificity, precision, *F*_1_-score, and area under the receiver operating characteristic curve, will be calculated for each diagnostic category to evaluate the app’s ability to detect skin-related NTDs. In parallel, we will conduct semistructured in-depth interviews with a purposive sample of 70-80 stakeholders, including policymakers, health care workers, community leaders, dermatologists, and members of leprosy-affected communities. Interviews will explore perceptions of the app’s usability, acceptability, and potential barriers and facilitators to its adoption within Senegal’s health system. Thematic analysis will be used to interpret qualitative data. Findings will help inform the design of an app-based intervention to be piloted in future community-level studies.

**Results:**

We expect the results to provide detailed insights into the feasibility and potential of the WHO Skin NTDs App to support and improve the detection of skin NTDs and common skin conditions at the community level in Senegal. We started data collection in August 2024, with the first results expected to be available in 2025.

**Conclusions:**

Our study will assess the performance and potential use of the WHO Skin NTDs App to detect skin NTDs and common skin conditions in Senegal, outlining its potential role in supporting early diagnoses and enhancing public health responses.

**Trial Registration:**

German Clinical Trials Register DRKS00034297; https://drks.de/search/de/trial/DRKS00034297/details

**International Registered Report Identifier (IRRID):**

DERR1-10.2196/69420

## Introduction

### Background

Neglected tropical diseases (NTDs) are estimated to affect more than 1 billion people worldwide, mostly in low- and middle-income countries [1]. With the NTD burden disproportionately high in disadvantaged communities, NTDs are rarely a priority in national and international health agendas or in the development of novel diagnostic tools or treatments [2]. To catalyze efforts, the World Health Organization (WHO) in 2020 set global targets to control and end the burden of NTDs by 2030 [1].

Skin NTDs are a subgroup of NTDs that manifest in lesions on the skin and can be detected by visual screening [3]. However, trained health care professionals who can reliably detect and diagnose such conditions are rare in many of the most affected settings [4]. Technological advancements are now promising to bridge this gap, especially in remote populations with limited access to resources [5-7].

In 2023, the WHO integrated 2 artificial intelligence (AI) algorithms into their existing WHO Skin NTDs App. Using a convolutional neural network approach, the algorithms classify images to identify skin conditions. Integrating AI into the app aims at further supporting frontline health workers in efforts to detect skin NTDs and other skin conditions at early stages of manifestation [8]. The app allows users to take images of a skin lesion on their smartphone and provides them with a list of potential diagnoses. The app uses 2 AI algorithms in a cascade. The first algorithm (Broad Skin Condition Screener) classifies images across 24 common skin conditions, included as individual diagnoses, and one group covering all 12 skin NTDs. If a skin NTD is flagged, the second algorithm (Skin NTD Classifier) identifies which of the 12 NTDs is most likely present (see Figure 1) [9]. Although the use of the AI component requires internet connection, images can be stored offline and uploaded at a later stage. Beyond the AI algorithm, the app also features an offline diagnostic decision tree with branching logic to assess symptoms, and app users can access a general learning section on skin conditions. Previous research has outlined the user-friendliness of these offline features, as well as their potential role in frontline health worker capacity building [10].

**Figure 1 figure1:**
[figure not shown]
Coverage of algorithms included in the World Health Organization (WHO) Skin NTDs App (beta version). *The Broad Skin Condition Screener algorithm does not differentiate between the 12 skin NTDs included in this category. Instead, if this category is flagged, users are recommended to use the Skin NTD Classifier for specific diagnosis suggestion. **During app development, Noma was not considered a skin NTD. In December 2023, the WHO changed their assessment and included Noma on their list of NTDs. NTD: neglected tropical disease.

The free-of-charge availability of the overarching Skin NTDs App presents a promising opportunity for large-scale implementation in resource-poor settings. However, the AI algorithm component so far has not been tested extensively in real-world applications [8]. Parallel to this study, the AI component is undergoing a first assessment in Kenya, with results expected before the end of 2025. Evaluations of other AI algorithm-based image analysis models for diagnosis have highlighted how performance differs across screened populations [11]. In general, variations in demographic characteristics, skin tones, and both the severity and complexity of skin conditions are likely to influence the detection accuracy [12]. Insights into potential avenues for implementing such algorithms in real-world detection efforts and for their integration into national programs are lacking [8].

To address these gaps, we will evaluate the performance of the WHO Skin NTDs App in the Senegalese setting. To assess the feasibility and acceptability of the app’s implementation, we are conducting qualitative interviews with stakeholders along the care cascade in Senegal. This is particularly critical for skin NTDs such as leprosy, where stigmatization of patients raises questions on the use of diagnostic tools at the community level [13,14]. Although early case detection might prevent disability and mitigate future stigma and psychological burden, maintaining diagnosis confidentiality is critical to protect patients.

### Study Objectives

The objective of our study is to investigate the potential of the AI component of the WHO Skin NTDs App (beta version) to support and improve the detection of skin NTDs and common skin diseases in Senegal. We will (1) evaluate the performance of the WHO Skin NTDs App algorithm in the detection of skin NTDs and common skin diseases and (2) qualitatively explore the feasibility and potential avenues for integrating the app into NTD detection processes at the community level. Our results will provide recommendations for the integration of this and similar tools into broader public health strategies to enhance the diagnosis and management of skin NTDs in Senegal and beyond.

## Methods

### Study Design

This study will combine quantitative and qualitative methods to evaluate the performance and potential of the novel AI diagnostic component of the WHO Skin NTDs App in the Senegalese context. This study protocol has been developed in accordance with the SPIRIT (Standard Protocol Items: Recommendations for Interventional Trials) guidelines (Multimedia Appendix 1).

The quantitative component will evaluate the performance of the AI algorithms integrated into the current beta version of the WHO Skin NTDs App. We will compare the algorithms’ suggested skin conditions with the diagnosis made by a dermatologist in the dermatology department of the Thiès regional hospital center.

The qualitative component aims at exploring the barriers, facilitators, and potential avenues for a larger scale implementation of the WHO Skin NTDs App. To this end, we will collect qualitative data from a range of key stakeholders, including policymakers, leaders and members of leprosy-affected communities, and medical professionals. Results are meant to inform the subsequent refinement of the app and the design and pilot testing of an intervention prototype.

### Study Setting

Skin NTDs are a major public health issue in Senegal, particularly in rural and underserved areas. The key skin NTDs in the country include Buruli ulcer, leprosy, yaws, onchocerciasis, cutaneous leishmaniasis, and scabies, which can lead to long-term disabilities, social stigma, and mental health challenges [1]. In Senegal, the management of NTDs is overseen by the National NTD Control Program, which is under the Directorate of Disease Control within the General Directorate of Public Health of the Ministry of Health and Social Action. To address skin NTDs, a multi-stakeholder approach is employed, which includes nongovernmental actors (eg, Action Damien, Raoul Foundation, DAHW), universities (Thiès, Dakar, Ziguinchor), and various government bodies. The focus of these stakeholders includes disease prevention, medical treatment, research, disability prevention, and rehabilitation.

Compared to other skin NTDs in Senegal, leprosy stands out due to its association with a long-standing isolation policy in the country. Although effective treatment and cure has been available since the 1980s, a law mandating the establishment of 9 social reclassification villages to isolate patients with leprosy was not repealed until 2023 [8,15]. As such, the discriminating character of the previous isolation policy continues to shape leprosy perception and stigma in Senegal. Many former social reclassification villages continue to exhibit active transmission, making them focal points of leprosy prevention activities in Senegal [16-18].

The Thiès regional hospital center, the study site for the quantitative evaluation of the app, is located approximately 70 km from Dakar in the regional capital of Thiès. As of 2023, the health system in the region serves approximately 2,340,000 inhabitants via a network of 335 health huts, 243 health posts, 10 private clinics, and 9 health centers [19]. Of the region’s 5 hospitals, 3 are public and 2 are private. Approximately 70% of the health posts are public [20]. The dermatology department of the Thiès regional hospital center, established in 2002, consists of a consultation room, a treatment room, a secretariat, and a hospitalization unit with a capacity of 9 beds. The department is staffed by 3 dermatologists, who consult with an average of 350 patients per week.

### Quantitative Component: Performance Evaluation of the AI Algorithm

#### Eligibility Criteria

The target population of this component will include any patient seeking treatment for a skin condition at the dermatology department of the Thiès regional hospital center during the study period. This also includes patients referred to the dermatology department from other departments or health facilities. Further inclusion criteria are (1) aged 1 year or older and (2) visible skin lesion on an unidentifiable part of the body. To maintain anonymity of patients, we therefore exclude patients with lesions on the face, fingers, or on or near identifiable scars or tattoos.

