#### Sample Size Calculation

Based on the sample size calculation for proportions, we determined that a sample size of 385 images is required to achieve a 95% confidence level with a margin of error of SE 5%, assuming an expected accuracy rate of 75%. In the absence of published performance metrics or internal validation results from the AI algorithm developers, we selected 75% as a conservative estimate of the algorithm’s expected accuracy for the purpose of sample size determination. We conservatively increase our target sample size from 385 to 800 to account for potential exclusions of images due to quality or identifiability concerns and to improve statistical power and robustness.

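### The anonymity exclusion is worded by patient although its purpose needs only a lesion-level rule, and the foreseen exclusion of images for quality is likely to make the app's performance look better than it is

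*Protocol article*

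**What the plan says.** All references are to the Protocol article.

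- **Eligibility Criteria (quantitative component).** The target population is "any patient seeking treatment for a skin condition at the dermatology department of the Thiès regional hospital center during the study period". The second inclusion criterion is a "visible skin lesion on an unidentifiable part of the body". The next sentence gives the reason, "To maintain anonymity of patients", and then the rule: "we therefore exclude patients with lesions on the face, fingers, or on or near identifiable scars or tattoos".
- **Sample Size Calculation.** The target is raised from 385 to 800 images "to account for potential exclusions of images due to quality or identifiability concerns and to improve statistical power and robustness". No expected rate of exclusion is given.
- **Recruitment and Data Collection (quantitative component).** The lesion of each eligible patient is photographed by a researcher with medical university training.
- **Outcome Measures and Data Analysis.** Confidence intervals come from the bootstrap, and the F1-score is emphasised because skin NTDs are expected to be the less common class.
- **Discussion.** The stated limitations are the single hospital department, prevalence that differs elsewhere, and possibly too few cases of some skin NTDs. Neither body site nor image quality is named. The same section says that severity and complexity are likely to influence accuracy, and that the work should inform use at community level.

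**The concern.** Two separate selections act on the images that are analysed.

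The first is by body site. The inclusion criterion works on the lesion and the exclusion on the patient. Someone with both an eligible and an ineligible lesion satisfies both sentences, so recruiters could decide either way. The patient-level rule discards people whom anonymity does not require to be discarded. Those people have lesions at more than one site, and some may have a skin NTD, the class in which the authors already fear small numbers.

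The second is by image quality. The app's AI component works from a photograph. A blurred or badly lit picture is one of the ways in which it can fail, and such pictures will also be taken by frontline health workers. If they are removed before analysis, the reported figures describe the app on good pictures only, yet they are meant to inform community use.

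**Working it through.** **1. The plan's own figure.** For one proportion, n = z² p(1−p)/d², with z = 1.96 and d = 0.05. At the stated p = 0.75 this gives 288.1, so 289; at p = 0.50 it gives 384.1, so 385. The stated 385 is therefore the 50% figure. That is a separate inconsistency, on the conservative side, and does not affect the present point.

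**2. Unit of exclusion.** The two sentences of the Eligibility Criteria, applied to four kinds of patient:

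| Lesions | Inclusion criterion | Exclusion as worded | Anonymous photograph possible? |
|---|---|---|---|
| Trunk only | met | not excluded | yes |
| Face or finger only | not met | excluded | no, under the plan's rule |
| Trunk and finger | met | excluded | yes, of the trunk |
| Trunk and face | met | excluded | yes, of the trunk |

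The sentences conflict only in the last two rows, and there the exclusion adds nothing to anonymity.

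**3. Effect of the body-site rule on accuracy.** The shift is f × g, where f is the share of target patients excluded and g is accuracy in included minus accuracy in excluded patients. The documents give neither, so both are assumed:

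- f = 10%: g = +10 points overstates accuracy by 1 point; g = −10 understates it by 1 point.
- f = 30%: g = +10 overstates by 3 points; g = −10 understates by 3 points.
- g = 0: no shift at any f.

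The sign is unknown.

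**4. Effect of quality exclusions on accuracy.** With a share x of images dropped, accuracy over all images is 0.75(1−x) + a·x, where a is accuracy in the dropped images. The 75% is the plan's planning value, used here for kept images; a and x are assumptions.

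| x | a = 75% | a = 50% | a = 0% (all failures) |
|---|---|---|---|
| 10% | 75.0% | 72.5% | 67.5% |
| 20% | 75.0% | 70.0% | 60.0% |

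In every cell 75% would be reported. The overstatement at a = 50% is 0.25x: 2.5 points at 10% and 5.0 points at 20%.

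**5. Comparison with random error.** The 95% half-width at 75% is 1.96 × √(0.1875/n): 4.3 points at n = 385 and 3.0 points at n = 800. With 20% of 800 dropped, n = 640 and the half-width is 3.4 points, less than the 5.0-point shift at a = 50%. Moving from 385 to 800 narrows the interval and leaves the shift where it was. A bootstrap of the kept images likewise reflects only sampling error.

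These figures concern accuracy. The effect on the F1-score also depends on how many dropped images show a skin NTD, which is not known.

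**The case against.** The case on the other side is substantial in four respects.

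- **A lesion-level reading is possible.** The exclusion is introduced as a consequence of the inclusion criterion, one lesion is photographed per eligible patient, and images are screened again for identifiability. The authors may have meant that only the photographed site matters. This stands as a reading, but the sentence does not say it, and the literal text excludes the patient.
- **Nothing shows that face or finger lesions are harder for the app.** A reader might infer that the body-site rule leaves an easier case mix. The documents do not support that: the Discussion names severity and complexity, not body site. The supported word is narrower.
- **Quality exclusions are only foreseen.** They appear as a contingency in the sample size, with no rate. Criteria for an unusable image may properly stand in an analysis plan that is not shown, and their absence is not criticised here. What remains is the stated intention to exclude on quality at all.
- **The inflation is not a forecast of loss.** A reader might take 1 − 385/800 = 52% as the planned loss and, with 50% accuracy in dropped images, arrive at 62.0%. The enlargement also serves power and robustness and covers identifiability, so 52% is only an arithmetic ceiling.

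It is also fair that pictures taken by a trained researcher in a hospital do not reproduce field quality, even if all are kept. That limits how much keeping them achieves, but gives no reason to drop the poor ones.

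**Conclusion.** The point holds in two parts of different strength. First, the exclusion and the inclusion criterion use different units. As worded, the exclusion loses patients who could be photographed anonymously. The case mix is narrower than the stated target population, the direction of any effect on performance is unknown, and scarce skin NTD cases may be lost. Second, excluding images for quality is likely to bias performance upwards, because poor pictures plausibly carry more failures.

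The documents do not allow the size of that bias to be estimated. The 2.5 and 5 points at 10% and 20% dropped rest on assumed accuracies of 75% and 50% and are illustrations. If dropped images were classified as well as kept ones, there would be no bias. Neither the larger sample nor the confidence intervals would reveal or correct it, and the stated limitations mention neither restriction.

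**What to change.** 1. State the exclusion by lesion site: photograph an eligible lesion where one exists, and exclude only patients with no lesion on an unidentifiable site. If this is already the practice, only the wording changes. If not, it needs a small amendment while recruitment is open. Table 1 ends quantitative collection in Q1 2025, whereas the Results section gives September 2025 for data collection as a whole. If recruitment has closed, report which rule was applied.
2. Run all non-identifiable images through the app and analyse them regardless of quality, counting no output as a failure. Report the quality-restricted result alongside, with quality graded blind to the app's output.
3. Limit conclusions to lesions on the eligible body sites, and add this to the limitations in the Discussion.

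Changes 2 and 3 concern analysis and reporting only, provided that the poor images have been kept. The cost is that the performance figures may be slightly less favourable. Anonymity is unaffected, since identifiable sites are still not photographed and identifiable images are still removed.

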#### Sample Size Calculation

Based on the sample size calculation for proportions, we determined that a sample size of 385 images is required to achieve a 95% confidence level with a margin of error of SE 5%, assuming an expected accuracy rate of 75%. In the absence of published performance metrics or internal validation results from the AI algorithm developers, we selected 75% as a conservative estimate of the algorithm’s expected accuracy for the purpose of sample size determination. We conservatively increase our target sample size from 385 to 800 to account for potential exclusions of images due to quality or identifiability concerns and to improve statistical power and robustness.

#### Recruitment and Data Collection

We will collect the images of skin lesions within the dermatology department of the Thiès regional hospital. Using the mobile survey tool Kobo Collect, we will take a picture of the skin lesion from every eligible patient. We will further record the diagnosis made by the dermatologist. We will further collect images of healthy skin from patients, defined as skin being free from dermatological lesions. Data will be collected by a researcher with medical university training. Skin lesion images and dermatologists’ diagnosis will then be linked to the suggested skin conditions from the WHO Skin NTDs App (see Figure 1). All images will be stored on a password-protected server, with access restricted to principal investigators and authorized researchers, ensuring participant data privacy and security.

#### Outcome Measures and Data Analysis

In our primary quantitative analysis, we will first evaluate the performance of the WHO Skin NTDs App’s AI component in detecting whether a skin condition belongs to the broader category of skin NTDs. Specifically, we will assess the Broad Skin Condition Screener, the first of the 2 AI algorithms. We will use the dermatologist’s diagnosis as the reference standard and calculate the following performance metrics:

Accuracy: proportion of total cases correctly classified as skin NTDs or skin conditions not caused by NTDs.Sensitivity (recall): proportion of actual skin NTD cases correctly identified by the algorithm (true positive rate).Specificity: proportion of skin conditions not caused by NTDs correctly identified as such (true negative rate).Precision: proportion of cases identified as skin NTDs that are truly skin NTD cases (positive predictive value).*F*_1_-score: harmonic mean of precision and sensitivity, providing a balanced measure of the algorithm’s ability to detect skin NTDs while minimizing false positives.Area under the curve: the algorithm’s ability to distinguish between skin NTD and skin conditions not caused by NTDs, derived from the receiver operating characteristic curve.

We anticipate a degree of class imbalance in our dataset, with skin NTDs being less prevalent than common non-NTD conditions. To mitigate potential bias from this imbalance, we will emphasize the *F*_1_-score. All performance metrics will be reported with 95% CIs, estimated using bootstrap resampling to reflect the uncertainty around our estimates. Our definition of correct prediction is as follows.

True positive: an image with any skin NTD is correctly classified as being a skin NTD.True negative: an image without a skin NTD is correctly classified as not being a skin NTD.False positive: an image without a skin NTD is incorrectly classified as being one.False negative: an image with a skin NTD is incorrectly classified as not being one.

We will assess the performance across 3 levels of AI prediction output from the app.

Top 1: only the app’s single most likely diagnosis is considered.Top 3: the app presents its 3 most likely diagnoses.Top 5: the app presents its 5 most likely diagnoses.

